## Methods and analysis

### Study design, setting and population

This is a randomised prospective phase III (therapeutic confirmatory) multicentre study. The trial population consists of patients undergoing robot-assisted laparoscopic upper urinary tract surgery. The trial will start at the University Hospital in Linköping, Sweden. After the start of the study, other Swedish hospitals will be invited to participate in the trial.

Inclusion and exclusion criteria for participation in the trial are shown in table 1.

**Table 1 T1:** Inclusion and exclusion criteria

Inclusion criteria	Exclusion criteria
The patient is listed for planned robot-assisted laparoscopic surgery on kidney and/or ureter at one of the hospitals participating in the trial The patient agrees to participate in the trial by signing ‘Informed consent’ after having received written and oral information	Anaesthetic risk classification (ASA) ≥4 Patients who are minors or declared incompetent, who have a severe psychiatric illness or cannot be expected to be able to understand the written and oral trial information due to severely impaired vision, hearing, cognition, reading ability or insufficient knowledge of Swedish Female patients who are pregnant or breastfeeding Premenopausal female patients who have not undergone sterilisation, hysterectomy, bilateral salpingectomy and/or bilateral oophorectomy, and who are not using highly effective contraception with low user dependence, and where there is no negative pregnancy test Emergency procedure Research staff is not available Extensive surgery on another organ during the same procedure The responsible anaesthesiologist recommends spinal or epidural analgesia Contraindications to morphine spinal, such as coagulopathy, previous back surgery with osteosynthesis material or severe aortic valve stenosis, or there is reason to expect a difficult puncture, such as pronounced scoliosis or pronounced obesity Contraindication to lidocaine infusion: proven allergy to local anaesthetics, renal failure with eGFR <30, liver failure due to acute hepatitis or cirrhosis corresponding to Child-Pugh ≥B, severe arrhythmia or heart failure problems (corresponding to NYHA IIIb or higher) and myasthenia gravis Previous participation in the trial

ASA, American Society of Anesthesiologists; eGFR, estimated glomerular filtration rate; NYHA, New York Heart Association.

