### Outcome measures

Primary and secondary outcome measures of this study are shown in table 2 with additional details provided in online supplemental table 1. The primary outcome measure of this study is QoR-15 on POD 1. Our primary hypothesis is that the reduction in QoR-15 from baseline before surgery to POD 1 is at least 8 points less in the morphine spinal group compared with the control group treated with intravenous lidocaine.

**Table 2 T2:** Primary and secondary outcome measures

**1**	**QoR-15 score at POD 1 (primary outcome measure)**
2	QoR-15 score preoperatively
3	QoR-15 score at POD 7
4	Pain (NRS) at rest and during motion 2 hours after arrival to the PACU
5	Pain (NRS) on POD 1–3
6	Pain (NRS) at rest and during motion on POD 7
7	Time from arrival in the OR to start of surgery
8	Time from end of surgery until leaving the OR
9	Incidence of unplanned termination of the lidocaine infusion
10	Amount of remifentanil in patients given remifentanil
11	Amount of intraoperative opioids in patients not receiving remifentanil, expressed in morphine equivalents
12	Length of stay at the PACU/ICU/HDU
13	Amount of opioids administered at the PACU/ICU/HDU during the first 24 hours after end of surgery
14	PONV requiring treatment at 0–6 hours and 6–24 hours postoperatively as well as during the whole postoperative stay
15	‘Time out-of-bed’ on POD 1–3
16	Amount of opioids administered during the first 24 hours at the PACU/ICU/HDU and in the ward
17	First POD passing gases
18	First POD passing stool
19	Incidence of pruritus
20	Length of stay
21	DAOH30
22	Postoperative complications until POD 30
23	Requirement for opioids after discharge
24	Incidence of respiratory depression leading to the use of a μ-antagonist within 48 hours of induction of anaesthesia
25	Intraoperative fluid balance
26	Time with low blood pressure during anaesthesia
27	Lowest MAP within 10 min after induction of anaesthesia
28	Highest MAP within 10 min of start of abdominal insufflation
29	Fraction of patients needing norepinephrine within 15 min after start of abdominal insufflation
30	Fraction of patients needing norepinephrine intraoperatively (later than 15 min after start of abdominal insufflation)
31	Average infusion rate of norepinephrine, in patients receiving norepinephrine, before 15 min after start of abdominal insufflation
32	Average infusion rate of norepinephrine, in patients receiving norepinephrine, after 15 min after start of abdominal insufflation

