33	Intraoperative Cardiac Index
34	Intraoperative Stroke Volume Index
35	Intraoperative Cardiac Power Index
36	Intraoperative dPmx
37	Intraoperative Pulse Pressure Variation
38	Intraoperative Stroke Volume Variation
39	Intraoperative dynamic arterial elastance
40	Intraoperative Systemic Vascular Resistance Index
41	Intraoperative heart rate
42	Biochemical markers of inflammation

DAOH30, Days alive and out of hospital at postoperative day 30; dPmx, A measure of contractility of the heart's left ventricle; HDU, high dependency unit; ICU, intensive care unit; MAP, mean arterial pressure; NRS, Numeric Rating Scale; OR, operating room; PACU, post-anaesthesia care unit; POD, postoperative day; PONV, postoperative nausea and vomiting; QoR-15, Quality-of-Recovery 15.

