#### Analysis groups

The primary outcome is analysed in the entire trial group according to the intention-to-treat (ITT) principle, except for the subjects who do not undergo the planned robot-assisted surgery within 12 months from inclusion, and/or neither receive intervention nor control treatment, and/or leave the trial and/or die before the POD 1 measurement. The clinical secondary analyses are also analysed in this entire trial group according to ITT. These analyses will be supplemented with:

A per protocol (PP) analysis of the primary hypothesis as well as NRS POD 1–3, where subjects who are included in the ITT analysis, however, without sufficient preoperative effect of the spinal analgesia, and/or where lidocaine infusion was prematurely terminated, and/or where the surgery was converted to an open procedure are excluded.An ITT and PP analysis as above where subjects with problematic pain are omitted. Problematic pain is defined here as preoperative opioid use for more than 1 month.

The haemodynamic and biochemical parameters are analysed only in the subgroup that is monitored with advanced haemodynamic monitoring according to the PP principle, that is, subjects with a spinal anaesthetic without adequate preoperative spread, and/or where lidocaine infusion was prematurely terminated, and/or where the surgery was converted to an open procedure are excluded.

Normal distribution will be tested with the Shapiro-Wilks test, except for QoR-15 and NRS data which are assumed to be not normally distributed. All significance tests are done two-sided. A p value lower than 0.05 is considered significant. No corrections for multiple comparisons are made unless otherwise specified.

Single missing values are in principle not imputed. In exceptional cases, if missing data cause an entire data series (in time) to be misleading, the missing data can be imputed with the average value of the two measurements closest in time, provided that this results in a reasonable value.

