#### Tests of significance

The primary outcome will be analysed using the Wilcoxon rank sum test (Mann–Whitney U test). For the secondary outcomes, comparisons of single-time values between groups will be analysed using Student’s t-test for normally distributed data, and Wilcoxon rank sum test (Mann–Whitney U test) for not normally distributed data. As mentioned above, QoR-15 and NRS are assumed to be not normally distributed. Proportions will be compared using the χ^2^ test. Longitudinal data such as pain on movement on POD 1 and 3 and perioperative haemodynamics will be compared using mixed effects models.

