Allowing different types of anaesthetic management can be considered a limitation, as this may introduce confounding effects. After discussion within the trial group, we decided to recommend intravenous anaesthesia; however, inhalational anaesthesia was permitted when preferred because of factors such as TCI(target controlled infusion)-related side effects or local clinical routines. We believe that permitting different anaesthetic regimens enhances external validity, enabling the results to be applied to a broader clinical context.

Strengths of the study include its multicentre design which increases external validity. Also, recovery is measured in multiple ways at multiple time points, as are effects on haemodynamic and inflammatory parameters. The use of an active comparator is a strength since it increases the clinical benefit of key results. The use of a control group (primary or secondary) without additional intervention has been contemplated but rejected for the following reasons:

The relevant question is not primarily whether morphine spinal is effective in this setting but whether it is more effective than alternative methods with fewer disadvantages.It is deemed not feasible to perform spinal analgesia blinded. This would require either the administration of morphine spinal after induction of general anaesthesia, which is not a preferred method since it might increase the risk of neurological injury related to the spinal punction, or it would require the omittance of bupivacaine which we feel is an important component of the morphine spinal concept. Therefore, the risk of confounding by placebo expectations is decreased when using an active comparator.It is ethically questionable to assign study patients to a treatment arm which we know is associated with severe postoperative pain.

In conclusion, the SMILe study will establish whether morphine spinal improves postoperative recovery compared with intraoperative lidocaine infusion in patients undergoing robot-assisted upper urinary tract surgery. Also, the effects of these two treatment modalities on haemodynamics and inflammation will be studied.

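### Every secondary result with p<0.05 counts as significant, with no default correction and no supportive or exploratory label for the 41 secondary outcomes

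*Protocol article*

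**What the plan says.** Under Analysis groups, the protocol article gives three consecutive rules that apply to all outcomes: "All significance tests are done two-sided"; "A p value lower than 0.05 is considered significant"; "No corrections for multiple comparisons are made unless otherwise specified".

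Tests of significance then carries testing into the secondaries: "For the secondary outcomes, comparisons of single-time values between groups will be analysed using Student’s t-test for normally distributed data", with rank tests, χ² tests and mixed models for the other data types.

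Table 2 under Outcome measures has 42 numbered rows. Row 1 is "QoR-15 score at POD 1 (primary outcome measure"). Rows 2 to 42 are secondary, ending with "Biochemical markers of inflammation". No row is marked as key, supportive or exploratory, and no testing order or correction appears elsewhere in the article.

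Analysis groups also repeats pain NRS on POD 1–3 per protocol, and repeats the ITT and PP analyses without patients with problematic pain. These are described as supplements to the ITT analysis.

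**The concern.** A per-test threshold applied to about 40 outcomes will produce some significant results by chance. That is harmless if readers are told that secondaries are supportive. Here the only stated status of a secondary result with p below 0.05 is that it is significant, in a trial described as follows: "This is a randomised prospective phase III (therapeutic confirmatory) multicentre study".

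What is at stake is the reading of a null primary. The Discussion says the trial will either support the benefit of morphine spinal or justify leaving it out, and it counts as a strength that "recovery is measured in multiple ways at multiple time points, as are effects on haemodynamic and inflammatory parameters". With no ranking, a stray difference in pain, opioid use, theatre times or an inflammatory marker could be presented with the same word, significant, as the primary result.

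Two rows also do not belong among the between-group tests. Item 2 is the preoperative QoR-15, which cannot be a treatment effect. Item 9 is unplanned termination of the lidocaine infusion, which has no counterpart in patients who receive the spinal.

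**Working it through.** **The plan's own figure.** The article states no error rate for the secondaries as a family. The only figure that uses alpha is the sample size. With difference 8, variance 400, two-sided 0.05 and 80% power:

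n per group = 2 × 400 × (1.960 + 0.842)² / 8² = 800 × 7.849 / 64 = 98.1, so 99. The exact t-test calculation gives 99.1, so 100.

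The stated 100 per group reproduces (one-sided 0.05 would give 78). The primary outcome is therefore planned at two-sided 0.05, and nothing below changes that.

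**Count of comparisons.** 42 rows − 1 primary = 41 secondary rows. Removing item 2 (baseline) and item 9 (lidocaine only) leaves 39 two-arm comparisons. Each row is counted once, although items 4 and 6 have pain at rest and in motion, item 14 has three time windows and item 42 an unstated number of markers.

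**Expected false positives, all 39 nulls true.** 39 × 0.05 = 1.95, whatever the correlation.

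**Chance of at least one.**
- Independent tests: 1 − 0.95^k. For k = 39 this is 1 − 0.135 = 0.865.
- Common correlation ρ, with c = 1.96: 1 − ∫ φ(u) [Φ((c − √ρ·u)/√(1−ρ)) − Φ((−c − √ρ·u)/√(1−ρ))]^k du.

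The correlations are assumptions; the article gives none.

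| True nulls k | Expected false positives | ρ = 0 | 0.3 | 0.5 | 0.7 | 0.8 |
|---|---|---|---|---|---|---|
| 41 | 2.05 | 87.8% | 75.2% | 57.7% | 37.8% | 28.2% |
| 39 | 1.95 | 86.5% | 73.8% | 56.6% | 37.2% | 27.8% |
| 30 | 1.50 | 78.5% | 66.2% | 50.7% | 33.9% | 25.6% |
| 14 | 0.70 | 51.2% | 43.8% | 34.8% | 24.9% | 19.7% |

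**Why k = 30 is shown.** The Introduction expects morphine spinal to be able to delay the start of surgery and to cause hypotension, nausea and itching. These bear on items 7, 14, 19, 26, 27 and 29–32, which is nine rows: 39 − 9 = 30. The row k = 14 is the smallest number of independent true nulls at which the chance passes one half.

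**A less uniform correlation.** If the 39 comparisons are grouped into ten mutually independent blocks (sizes 5, 5, 5, 4, 3, 3, 2, 2, 8, 2; an assumed grouping), the chance is 80.1%, 73.4% and 60.9% at within-block correlations of 0.5, 0.7 and 0.9.

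**The case against.** The strongest reply is that nothing is stated wrongly. The rule is per comparison and delivers 5% per comparison; the article claims no family-wise control over the secondaries. One outcome is named primary, and it alone drives the sample size and the interim stopping rule. Uncorrected secondaries are common, and the label confirmatory describes the trial's phase, not each row of Table 2. All of this stands. A reader might infer that the trial's type I error for its main question is inflated by this rule; the documents do not support that. The repeated interim testing of the primary outcome is a separate matter.

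A second reply is that the sentence says corrections are not made unless otherwise specified, and a full protocol, a SAP and the online supplement are not shown. This also stands in part: correction is the absent default, not something ruled out. But the point does not rest on a missing detail. The article itself fixes both the threshold and the meaning of crossing it, and it shows no exception.

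A third reply concerns size. A reader might infer that at least one false significant result is more likely than not, or that the figures are lower bounds. Neither holds generally. Extra tests within rows push the chance up, but real effects and correlation push it down. Several haemodynamic rows come from one device, the opioid rows overlap, and length of stay overlaps with days alive and out of hospital. Under a common correlation of 0.7 or 0.8 the chance is 37% or 28%. Among the secondaries only pain NRS on POD 1–3 is clearly repeated across analysis sets; those repeats are highly correlated and add little.

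Finally, no passage says that a secondary may rescue a null primary. That is true, but no passage prevents it either.

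**Conclusion.** The point holds as a cheap improvement in wording, not as an error in the primary analysis. The article applies one declaration of significance to the primary and to 41 unranked secondaries, so a null primary could be followed by secondary results reported as significant effects.

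If all 39 two-arm nulls were true, about two such results would be expected by chance, and the probability of at least one would run from 86% (independent) through 57% (ρ = 0.5) to 28% (ρ = 0.8). With nine rows set aside as plausibly real effects, the same range is 79%, 51% and 26%. Both the correlations and the number of true nulls are assumptions, so these figures show the order of magnitude only. Across the assumptions shown, the chance of a spurious significant secondary is several times the 5% that a reader might attach to the word.

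**What to change.** Replace the no-correction sentence under Analysis groups, and limit the preceding 0.05 sentence to match, with wording such as:

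*The overall two-sided 5% level, across the interim and final analyses, applies to the primary outcome in the ITT set only. PP analyses and analyses without problematic-pain patients are sensitivity analyses. Secondary outcomes are supportive/exploratory and are reported as between-group estimates with unadjusted 95% confidence intervals, without declarations of significance.*

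The word *overall* matters: the sentence must not be read as granting a fresh 5% at each of the analyses after 100 and 150 patients and at the end.

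Report item 2 as a baseline characteristic (it is still needed to calculate the change in QoR-15), and item 9 descriptively in patients given lidocaine. Testing a few named secondaries in a fixed order after a significant primary is an option for the sponsor, not part of the required change.

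Cost: no extra patients or data and no loss of power for the primary. Isolated secondary p-values could no longer be presented as confirmed effects. The Ethics section says substantial protocol changes go through CTIS, so a protocol wording change may need submission unless it is placed in the SAP before the code is broken. There is time: Trial status reports 54 of the planned 220 patients included by 1 October 2025, and Blinding says the code is broken only when data acquisition is complete.

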#### Tests of significance

The primary outcome will be analysed using the Wilcoxon rank sum test (Mann–Whitney U test). For the secondary outcomes, comparisons of single-time values between groups will be analysed using Student’s t-test for normally distributed data, and Wilcoxon rank sum test (Mann–Whitney U test) for not normally distributed data. As mentioned above, QoR-15 and NRS are assumed to be not normally distributed. Proportions will be compared using the χ^2^ test. Longitudinal data such as pain on movement on POD 1 and 3 and perioperative haemodynamics will be compared using mixed effects models.

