**Methods and analysis:**

In this randomised, assessor-blinded multicentre trial, 220 patients scheduled for robot-assisted upper urinary tract surgery under general anaesthesia are recruited after obtaining informed consent. They are randomised to receive either intrathecal analgesia or an intraoperative infusion with lidocaine. The primary study outcome is the decrease in QoR-15 from baseline to postoperative day 1. Other outcomes of interest include postoperative pain, length of stay and postoperative complications. Differences in intraoperative haemodynamics and postoperative inflammatory parameters will also be analysed.

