### Inclusion and randomisation

Test subjects are included consecutively. Randomisation of the participating subjects takes place after inclusion in the trial, before the start of anaesthesia. For each participating hospital (apart from US Linköping, see the next section), Forum Östergötland prepares before the start of the trial 100 sequentially numbered, opaque and sealed envelopes in series of 20 with both groups distributed 1:1. For US Linköping, 200 envelopes are prepared in the same way. Forum Östergötland retains the randomisation codes.

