### Statistics

#### Calculation of sample size

In a previous feasibility study including 30 patients undergoing robot-assisted upper urinary tract surgery under general anaesthesia without morphine spinal or intravenous lidocaine, QoR-15 decreased from a median (IQR) preoperative value of 141 (128 – 145) to 106 (88–103) on POD 1 (means (SD) 136 (11) and 105 (22); unpublished data). We assume that variance ((SD)^2^) is 400 in both groups on POD 1. With an MCID of 8, a desired alpha value of <0.05 and a power of 80% 100 subjects are needed in each group (GPower V.3.1.9.7, Heinrich-Heine-Universität Düsseldorf, Germany). To compensate for dropouts, a total of 220 subjects will be included in the trial.

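### The primary outcome is defined both as the POD 1 QoR-15 score and as its change from baseline, and the planned rank-sum test does not say which is ranked or adjust for baseline or site

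*Protocol article*

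**What the plan says.** All of the following stands in the current text of the protocol article.

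- Abstract, Methods and analysis: "The primary study outcome is the decrease in QoR-15 from baseline to postoperative day 1".
- Outcome measures: "The primary outcome measure of this study is QoR-15 on POD 1". Table 2, item 1, agrees: "QoR-15 score at POD 1 (primary outcome measure".
- Outcome measures, the sentence after that definition, on the hypothesis: "the reduction in QoR-15 from baseline before surgery to POD 1 is at least 8 points less in the morphine spinal group".
- Calculation of sample size: the variance is set at 400 for the POD 1 values, and "With an MCID of 8, a desired alpha value of <0.05 and a power of 80% 100 subjects are needed in each group".
- Tests of significance: "The primary outcome will be analysed using the Wilcoxon rank sum test (Mann–Whitney U test". No covariate or stratum is named. Under Analysis groups, "All significance tests are done two-sided", and QoR-15 is assumed not to be normally distributed.
- Interim analyses: after 100 and 150 operated patients the trial stops if the primary outcome measure differs significantly. No variable is named there either.
- Inclusion and randomisation: each hospital has its own envelopes, "100 sequentially numbered, opaque and sealed envelopes in series of 20 with both groups distributed 1:1" (200 at Linköping). Allocation is therefore blocked within site.
- Interventions and measurements: baseline QoR-15 is collected before the day of surgery.

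**The concern.** The score and the change are different variables with different variances, so the same rank-sum test can give different p-values on the same patients. If both remain on paper, the trial, which describes itself as confirmatory, has no single prespecified primary test, and a choice could be made once data are seen. The interim rule makes this pressing, because stopping recruitment depends on the significance of a variable with two definitions.

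There is a second, smaller issue. Baseline QoR-15 is measured and allocation is blocked by hospital, yet the named test uses neither as an adjustment. The hypothesis is stated in QoR-15 points, while a rank-sum p-value alone gives no estimate in points.

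**Working it through.** **Inputs from the article:** difference 8; two-sided alpha 0.05; power 80%; POD 1 SD √400 = 20; feasibility SDs 11 (baseline) and 22 (POD 1). **Assumption:** the correlation r between baseline and POD 1 is not given, nor is the SD of the change, so r is varied.

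**1. The plan's own figure.** n per group = 2(1.960 + 0.842)² × SD² / 8² ≈ 0.245 × SD². With SD 20 this is 98.1, so 99. The exact t-test gives 99.08, so 100. The stated 100 therefore reproduces, for an unadjusted t-test on the POD 1 score. For a rank-sum test on normal data, 99.08 / 0.955 = 103.7, so 104 per group (power about 78.5% at 100). That total of 208 still fits within 220.

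**2. The same formula for each candidate variable.**
- Change: SD = √(11² + 20² − 2r × 11 × 20) = √(521 − 440r).
- POD 1 adjusted for baseline: SD = 20√(1 − r²).

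| r | Score: SD, n | Change: SD, n | Baseline-adjusted: SD, n |
|---|---|---|---|
| 0 | 20.0, 99 | 22.8, 128 | 20.0, 99 |
| 0.3 | 20.0, 99 | 19.7, 96 | 19.1, 90 |
| 0.5 | 20.0, 99 | 17.3, 74 | 17.3, 74 |

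Score and change break even at r = 121/440 = 0.275. Below that the change is the noisier variable; above it the score is.

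**3. Rank-sum tests on both variables.** Simulation: 10,000 trials per cell, 100 per group, bivariate normal data, SDs 11 and 20.

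| r | Power, score | Power, change | Verdicts differ (8-point effect) | Type I error if either counts |
|---|---|---|---|---|
| 0 | 78.6% | 67.3% | 16.9% | 7.3% |
| 0.1 | 78.1% | 71.2% | 14.6% | 7.7% |
| 0.3 | 78.8% | 79.7% | 13.8% | 7.6% |
| 0.5 | 77.7% | 88.5% | 14.4% | 7.6% |

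Smaller separate runs agree within a point or two (change power 66 to 89%, disagreement up to 18%). Each test alone holds about 5%. The last column is for a single analysis and takes no account of the interim looks.

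**4. Site.** Assumptions: three sites of 120, 40 and 40 patients, site SD 8, blocks of 20. The unstratified rank-sum tests have type I error of about 3.8 to 4.5%. Power on the POD 1 score is about 75 to 76%, against about 78 to 80% with no site effect. A linear model with baseline and site has about 80 to 90% for r from 0.1 to 0.5.

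**5. Why one adjusted model settles the definition.** The change is the POD 1 score minus baseline. In a linear model that contains baseline, replacing the score by the change lowers the baseline coefficient by exactly 1 and leaves the treatment coefficient and its standard error as they were. If the outcome is written as a decrease, only the sign flips.

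**The case against.** **Baseline is not simply ignored.** If the change is ranked, baseline enters by subtraction. This stands: only the raw score leaves baseline out altogether. What neither version does is adjust for it as a covariate.

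**A rank test was chosen because QoR-15 is expected to be non-normal, and the linear model's power advantage depends on shape.** This also stands. A reader might infer that the linear model wins at any correlation. That holds for precision against unadjusted means, not for power against rank tests. With POD 1 SD 22, r = 0.3 and moderate left skew (assumed), two simulations gave power for score rank test / change rank test / linear model of 81/81/79% and 79/80/76%. With stronger skew one gave 87/85/76%. The article does not show the shape at POD 1; the feasibility mean and median there are close (105 and 106).

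**The size of the problem depends on the SD.** With the feasibility SD of 22, rank-sum power on the score is about 69 to 72%. The plan assumes 20, which gives about 77 to 79%. That gap concerns the SD, not the choice of test, so the figures here use 20.

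**Omitting site is harmless to validity.** Correct: it makes the test slightly conservative.

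**The missing details may be elsewhere.** A statistical analysis plan and the online supplementary table are not shown, and a rank-sum test can be reported with a Hodges-Lehmann shift in points. This answers the lack of an effect estimate and weakens the adjustment point. It does not answer the contradiction: whichever variable such a document names, it would overrule a statement printed in this article.

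**Conclusion.** The contradiction in the primary outcome is real and must be corrected. On the plan's SD of 20, with normal data and r between 0 and 0.5, the choice of variable moves rank-sum power from about 77 to 79% (score) to anywhere between about 67 and 88% (change). It alters the verdict in about 14 to 17% of trials with a true 8-point effect. That percentage is disagreement, not an error rate; the error-rate cost is about 7 to 8% instead of 5% if either version may count as success.

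Adjustment for baseline and site is a cheap improvement and not the repair of an invalid test. Some stronger readings are not supported. The sample size is not arithmetically wrong. Neither version is biased, since under randomisation both target the same mean difference. The rank-sum test is not invalid for lacking site. Nothing in the article shows that the sponsor intends to choose between the two; it only leaves that possible.

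**What to change.** Before the first interim analysis (100 operated patients; 54 had been included by 1 October 2025), name one primary variable and use it in the abstract, Outcome measures, Table 2, Calculation of sample size, Tests of significance and Interim analyses.

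Analyse POD 1 QoR-15 adjusted for baseline QoR-15 and site, and report the difference in points with a 95% CI. There are two acceptable routes:

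- **Linear model with robust standard errors.** It gives the same treatment estimate for score and change. Add a site-stratified rank test (van Elteren) as sensitivity analysis. The existing sizing is conservative for this model under the plan's SD, since 99 per group is its requirement at r = 0.
- **Rank-based or ordinal primary analysis**, if the sponsor prefers it because of expected non-normality: a version adjusted for baseline and site, such as a proportional-odds model, with an estimate in points alongside.

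If an unadjusted test of the change were kept instead, the sample size would have to be restated with the SD of the change, which the feasibility data should supply.

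**Cost:** wording and a protocol modification; every variable is already collected. **Downside:** under skew the linear model can lose power to the better of the two rank tests, by a few points in the moderate case above and by about 11 (87 against 76%) in the strongly skewed one.
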